### Enhanced screening vs standard screening conditions

The “enhanced” screening condition is implemented in 25 of our 50 PHC catchment areas, allowing us to examine whether the added community-based screening through community health fairs a) increases identification of patients with co-morbid diagnosis (Table 1); and b) improves linkage to and retention in care, compared to co-morbid patients identified via standard PHC-based screening. Specific recruitment procedures for each setting are described below, followed by common screening procedures and tests.

**Table 1 Tab1:** Initial and Confirmatory Screening Criteria

Screening stage	Inclusion criteria at each stage
Initial Screening Inclusion Criteria *Enhanced screening (health fair or PHC)* *Standard screening (PHC only)*	*Age:* 30 years or older *Mental competency:* Modified Short Blessed Cognitive Test [103] score ≤7 *General psychological distress*: The Kessler-10 [81] score ≥6 *One or more of the following cut-off measures for diabetes, hypertension, and/or CVD:* • Capillary Blood Sugar ≥160 mg/dL • Blood pressure ≥ 140/90 mmHg • Possible Angina: Rose angina questionnaire [104]^a^ • Self-reported physician-diagnosed history of DM, hypertension or ischemic heart disease
Confirmatory Screening Inclusion Criteria (PHC only)	*Depression/anxiety*: The Mini-International Neuropsychiatric Interview (MINI) [82] *One or more of the following clinical measures for diabetes, hypertension, and/or CVD:* • Blood pressure ≥ 140/90 mmHg • Capillary blood sugar ≥160 mg/dL • Physician-diagnosed history of DM, hypertension or ischemic heart disease (patient must show prescription or medication) • Possible rose angina^b^
Exclusion Criteria	• not mentally competent to provide consent per the standard screener [103], answer to study measures and/or participate in the intervention. • Participants who do not provide contact information

^a^ Patients who screen negative for hypertension and DM, but have possible angina on the rose angina questionnaire will be invited to the confirmatory screening

^b^ Patients who screen positive on the rose angina measure at initial screening and positive on the MINI during the confirmatory screening, but negative on hypertension and DM are marked as tentatively enrolled on the confirmatory screening form. At the baseline assessment electrocardiogram and cholesterol to check for CVD will confirm eligibility

At the enhanced screening PHCs, nurses and ASHA run health fairs in villages that are a part of our collaborating PHC catchment areas. Prior to conducting the fairs, ASHAs raise awareness and provide outreach of the upcoming health fair through announcements at community events and meetings, poster, brochures, and door-to-door visits to community members. One health fair is held per week during the five-week recruitment period. The health fair provides an opportunity for people in the community to receive a free health check-up.

Screening occurs in two phases, during the initial screening and confirmatory screening (Table 1). The initial screening is held at the health fair or at the associated PHCs in the enhanced screening condition and at the PHC only for the standard screening condition. Interested patients give written informed consent to study staff for the screenings, and those meeting the eligibility criteria during the initial screening are invited to a confirmatory screening at the PHC. Patients who meet the eligibility criteria during the confirmatory screening are invited to participate in the study. Eligible participants receive information about the study verbally as well as in written form if literate, including details about the intervention, study protocol, randomization process, time commitment and potential risks and benefits. Participants are informed that participation is voluntary, there are no negative consequences for refusing to participate, and that consent can be withdrawn at any time during the study without any repercussions. Participants receive a copy of the study information sheet and informed consent. Illiterate participants have an option of providing verbal consent or a thumb print. In those cases, a witness, unaffiliated with the study, also signs the consent form.

#### Inclusion and exclusion criteria

Participants, who are 30 or older, with co-morbid CMD (Depression or Anxiety Disorder) and either hypertension, diabetes, or ischemic heart disease, and who are willing and able to consent and be followed for 12 months are considered eligible for inclusion in the study.

### Collaborative care intervention design

The proposed multi-level “Healthy Living” intervention has been designed to promote long-term mental and physical health among the participants, by training PHC staff and ASHAs in the collaborative, stepped care model and by providing patients with skills that can be incorporated into their lifestyles. The stepped care model includes referrals of suicidal patients to the district psychiatrist and additional referrals for abnormal lab values, and the support of our psychiatry consultants during their weekly calls. The content and format are guided by our conceptual model [64, 66, 69, 70] and include strategies that can be easily integrated into existing health care structures and that have been found effective in previous studies [27, 28, 32, 39, 55, 59, 60, 69–77].

#### Collaborative care staff training

Staff in the 25 intervention PHCs receive training sessions in the collaborative care model [26] by psychiatrists from St John’s Medical College, who have volunteered to take on the role of “consultant psychiatrist” [78]. The PHC staff training is designed to enable them to effectively integrate treatment of CMDs into their regular practice in patients with co-morbid medical conditions. A modified version of the IMPACT model [48, 78] was adapted for our setting to maximize the likelihood of sustainability. PHC staffs are required to undergo one full day of interactive group training. The morning session trains all PHC staffs on management of chronic non-communicable diseases at the clinic level and the second half focuses on collaborative care in mental health. Primary care physicians are trained to identify and treat patients presenting with a CMD. The PHC nurses are trained to function as “care managers,” and help with tracking patient progress. Support is also being provided by the consulting psychiatrists, who provide both routine caseload, diagnostic, and treatment consultation for difficult cases, which may include referral recommendations when additional care is needed. Other care team members include the PHC pharmacist, trained to educate patients and their caregivers about their medication regimen, side effects and adherence. Finally, the ASHAs are trained in risk factor screening and modification, and act as a liaison between the PHC, patients, families and community. They co-facilitate the healthy living groups and provide appointment reminders through home visits.

#### Clinic-based intervention

Participants in the 25 intervention PHCs, receive diagnostic test and clinical treatment for both their mental illness and chronic disease by the PHC care team trained in comprehensive integrated mental health and CVD care using the stepped collaborative care model described above [39, 74].

#### Community-based intervention

Participants in the intervention PHCs are given an appointment to participate in a 12-month, healthy living group, designed to target risk factors important in management of depression, anxiety, DM, and CVD (Table 2). Each group includes eight to 10 same-sex participants and held in an easily accessible venue in the community. The first 12 weekly sessions are facilitated by a master’s level counselor and co-facilitated by an ASHA, who subsequently provides nine monthly sessions focused on behavior maintenance. The behavioral change strategies used are based on principles of social cognitive theory, such as observational learning, setting manageable goals, practice and getting feedback, building self-efficacy and skills training [69, 70].

**Table 2 Tab2:** Community-based Healthy Living Group Session Topics and Exercises

Session #	Topics covered	Exercises
1	CVD risk factors and diabetes	Discuss modifiable and non-modifiable behavioral risks
2	Psychological well-being, depression, anxiety and stress	Identify sources of and strategies to reduce depression, anxiety, and stress
3	Role of nutrition in disease	Review eating habits and develop plan to eat healthier
4	Improving physical and emotional health with exercise	Strategies for overcoming obstacles and creating a habit to exercise on a regular basis
5	Smoking and smokeless tobacco cessation	Discuss harmful effects of tobacco, triggers, and strategies for quitting
6	Alcohol use	Discuss harmful effects of alcohol, triggers, and strategies for quitting
7	Social support for behavior change	Sources of emotional, practical, and informational, strategies for approaching family, friends, and community for support, identify social support needs. Communication skills to use with unsupportive people.
8	Quality of life	Assessing quality of life and identifying strategies to improve quality of life
9	Tools for initial behavior change	Self-monitoring, goal setting, self-reinforcement, setting up an environment that supports change
10	Review of sessions 1-9	Identify successes and barriers to behavior change
11, 12	Long term maintenance of behaviors. Different strategies needed for initial change	Setting and reaching behavior change goals by using strategies learned in previous sessions
Monthly	Behavioral maintenance session	Review accomplishments, problem solving barriers, revising plans, utilizing group support

#### Session format

Each begins with breathing exercises for relaxation known to be effective in both CMD and CVD [79, 80]. The interrelationship between thoughts, emotions, behaviors and their impact of health are discussed to set the stage for the introduction of cognitive techniques. A list of common stressful life situations are developed by the group and used as examples for subsequent problem-solving skills training and coping skills training. Participants are encouraged to set both short term and longer-term goals and to make a commitment to change at the end of every session and reviewed and reinforced in the following-section. In addition, participants are also encouraged to set up buddy systems within the group and establish informal peer support networks.

We anticipate that our integrated intervention will have both direct and indirect beneficial effects on the families and communities associated with the Intervention PHCs. ASHAs involved with the integrated intervention groups meet with every participant’s family during bi-monthly home visits and encourage them to support the participant’s new healthy lifestyle. Participants themselves are encouraged to act as dissemination agents by sharing the knowledge and skills learned during the Healthy Living groups with their families.

Implementation and adherence to intervention protocols are documented and monitored through weekly reports of HLG sessions, weekly psychiatry consultation calls between PHC medical officers and the consulting psychiatrist, and through observation of the intervention sessions by an independent monitor who completes a check-list to ensure that all components are covered. In addition, the intervention coordinator makes weekly visits to the PHCs to ensure that all participants are appropriately referred for care. All intervention staff are trained and certified in all components of the intervention.

### “Enhanced” standard treatment

All staff in the PHCs that have been randomized to Enhanced Standard Treatment will receive a full day of basic training in established clinical protocols set by the state of Karnataka. For ethical reasons, since standard PHC treatment often includes inappropriate use of vitamins and anxiolytics, a psychiatrist leads the afternoon session training on how to treat CMDs per standard treatment protocols.

Patients in the standard treatment arm will receive usual care per the standardized protocols developed by the State. We will also ensure that any patient who is diagnosed as moderately to severely depressed has access to effective anti-depressant medication by referring eligible patients to a psychiatrist located in the nearest district hospital. Patients identified as at high risk for suicide are also referred to district hospital psychiatrists at screening and assessments per study protocol. In addition, any abnormal clinical results (e.g. hypertension, DM, etc.) found at screening and cohort assessments receive an appropriate referral.

### Outcome measures and schedule

The vast majority of the study measures have been used previously in India. Remaining measures (internalized stigma of mental illness, patient satisfaction and clinical vignettes), were adapted and pilot tested during our start-up phase to ensure that they are appropriate for our specific study population and setting. All measures have been translated into Kannada and back translated.

All cohort participants are assessed at baseline, 6 weeks, 3 months, 6 months and 12 months. To minimize attrition, we collect extensive contact information from all participants at enrollment. This includes mobile phone numbers, as well as street addresses, information about landmarks, and the name and phone number of someone who always knows how to reach them. This information is verified and updated during each assessment visit, HLG sessions visit and tracking phone calls and visits. All research materials will be coded with ID numbers only and linked to contact information on a separately stored document kept under lock and key.

To examine if community-based health fair screenings increases subsequent diagnoses in the PHC of patients with co-morbid mental health and chronic disease diagnoses, we use the Kessler-10 [81], MINI [82], and the clinical measures for diabetes and CVD outlined in Table 1. To screen for psychological distress at the initial screening using the Kessler-10, a brief standardized questionnaire that correlates with other commonly used depression screening questionnaires and with the DSM IV diagnoses of both depression and anxiety disorders [81, 83]. At the subsequent confirmatory screening, MINI is used to confirm the diagnosis of anxiety or depressive disorder as per DSM-IV guidelines. We also assess suicidal ideation based on items from the MINI and refer participants at high suicidal risk to the district psychiatrist for further management and treatment.

Linkage and retention in care is measured by the proportion of participants who started treatment and the proportion of these participants who were retained in care throughout the study.

To evaluate the effects of the clinic and community-based intervention for co-morbid primary care patients compared to the enhanced standard treatment services we measure severity of anxiety and depressive symptoms, blood pressure, body mass index and measures for diabetes and cardiac conditions (Table 3).

**Table 3 Tab3:** Outcome measures and study schedule

Measure	Screening	Baseline	6 weeks	3 months	6 months	12 months
Clinical Measures						
Systolic blood pressure	X	X	X	X	X	X
Diastolic blood pressure	X	X	X	X	X	X
Blood sugar	X					
BMI (weight/height)	X	X				X
Weight		X	X	X	X	X
Waist circumference		X	X	X	X	X
Electrocardiogram		X				X
Total cholesterol (with lipid profile)		X		X	X	X
LDL (Lipid profile)		X		X	X	X
HDL (Lipid profile)		X		X	X	X
Triglycerides (Lipid profile)		X		X	X	X
Glycosylated hemoglobin		X		X	X	X
Serum creatinine		X		X	X	X
Urine creatinine		X				X
Urine microalbumin		X				X
Questionnaires						
Rose angina questionnaire [104]	X					
The Kessler-10 [81]	X					
Modified Short Blessed Cognitive Test [103]	X					
MINI [82]	X					
PHQ-9 [85]		X	X	X	X	X
GAD-7 [84]		X	X	X	X	X
Patient perception					X	X
Fagerstrom Test for Nicotine Dependence (FTND) and FTND-Smokeless Tobacco [105, 106]		X	X	X	X	X
Alcohol Use Disorders Identification Test (AUDIT) [107]		X	X	X	X	X
Food Frequency [108]		X				X
International Physical Activity (IPAQ) [109]		X		X	X	X
Medication adherence (VAS) [110]		X	X	X	X	X
Diabetes self-management questionnaire [111]		X	X	X	X	X
World Health Organization (WHO) Disability Assessment Schedule 2.0		X				X
Demographics		X	X	X	X	X
Social support [112]		X		X	X	X
WHO Quality of life (WHOQOL-BREF) [113]		X			X	X
Integrated Stigma for Mental Illness Scale (ISMI) [114]		X		X	X	X

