The protocol described in this article is an ongoing randomized controlled-trial to implement and evaluate a multi-level community based collaborative care model in rural Ramanagaram district in the state of Karnataka, to improve screening, diagnosis, and treatment of depression in India among patients with co-morbid CMD and either DM or CVD at PHC. The aims of our study are; 1) To examine if community-based screenings for depression, anxiety, DM and CVD risk factors during community health fairs (a) increase subsequent diagnosis of these disorders in PHCs; and/or (b) lead to better linkage and retention in care as compared to the standard PHC based screening. We are using accredited social health activists (ASHAs) to raise awareness and provide outreach for the community health fairs; 2) Implement and evaluate the effects of providing staff training to PHC staff in the collaborative care model of integrated mental health (depression and anxiety) and chronic disease (hypertension, DM, and CVD) as compared to the enhanced standard care model. In addition, we are implementing a community-based risk factor reduction groups (Healthy Living Intervention), co-facilitated by ASHAs, to target risk factors common to both mental illness and chronic physical disease, with group session topics in exercise, diet, adherence to medical regimens, ocial support, coping skills, and problem solving skills; 3) evaluate the effects of the clinic and community-based intervention for co-morbid primary care patients compared to the enhanced standard treatment services.

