#### Screening

To test the hypothesis that, compared to standard screening, enhanced screening will result, on an average, in more people being identified as co-morbid for CMD and CVD/DM during the confirmatory testing at the PHC, we will use a Poisson regression model - or in case of over dispersion, a negative binomial model - with PHC as the unit of analysis, and population size in the catchment area of the PHC included as an offset.

Secondary analysis will explore subsequent linkage and retention in care of enrolled participants first screened at the community health fairs compared to those first screened at PHC. These participants will be compared by examining the proportion of participants who started treatment both by the 6 week follow-up, as well as the proportion retained throughout the study. We will use a mixed-effects logistic regression model with a random intercept for PHC.

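### Retention in care is defined among treatment starters, a group formed by the linkage outcome that screening is meant to change, and the analysis section does not state a denominator

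*Protocol article*

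**What the plan says.** Three places in the Protocol article bear on this.

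- **Outcome measures and schedule** gives the only operational definition. Linkage is the proportion who begin treatment, and retention is "the proportion of these participants who were retained in care throughout the study". The natural antecedent in that phrase is those who started treatment.
- **Statistical analyses, Screening** sets a secondary, exploratory analysis in "retention in care of enrolled participants first screened at the community health fairs compared to those first screened at PHC". The quantities compared are "the proportion of participants who started treatment both by the 6 week follow-up, as well as the proportion retained throughout the study", in a mixed-effects logistic model with a random intercept for PHC. No denominator is attached to the retention proportion.
- **Background** (aim 1b) asks whether community screening will "lead to better linkage and retention in care as compared to the standard PHC based screening". **Enhanced screening vs standard screening conditions** repeats the question: whether the added screening "improves linkage to and retention in care, compared to co-morbid patients identified via standard PHC-based screening".

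Table 1 and the text after it say that initial screening in the enhanced condition takes place at a health fair or at the associated PHC. In the standard condition it takes place at the PHC only.

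**The concern.** Starting treatment is one of the two outcomes on which the screening groups are compared, and the trial hopes that screening will move it. A regression for retention fitted only to starters therefore uses a subset whose make-up may depend on how people were screened. Even if screening had no effect on anyone's persistence in care, the two sets of starters could differ, and so could their retention.

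What is at stake is the retention half of aim 1(b). Under a starters-only denominator, a group that links more people, some of whom persist less well, can appear worse at retention although a larger share of its enrolled participants stays in care. A group that links fewer people can appear better. Because the analysis section does not say which denominator enters the model, the choice could also be made after results are seen.

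**Working it through.** **Plan's own figure.** There is none to reproduce. The document gives no linkage rate, retention rate or power for this comparison. Every rate below is an assumption that shows direction only.

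**Text side by side.**

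| Place | Population | Retention denominator |
|---|---|---|
| Outcome measures and schedule | participants | those who started treatment |
| Statistical analyses, Screening | enrolled participants | not stated ("as well as the proportion retained throughout the study") |

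The second entry reads most easily as all enrolled, but it does not say so. The same sentence compares "the proportion of participants who started treatment both by the 6 week follow-up", so starting treatment is an outcome of the comparison as well as the gate into the first denominator.

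**Formula.** Let *s* be the proportion of enrolled participants who start treatment and *r* the proportion of starters retained, with F for fair and P for PHC as place of first screening.

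- Among starters: D_c = r_F - r_P
- Among enrolled, non-starters counted as not retained: D_e = s_F r_F - s_P r_P

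If s_F = s_P = s, then D_e = s x D_c, and the signs must agree. If r_F < r_P, then D_e is positive exactly when s_F / s_P > r_P / r_F. So a reversal needs start rates and starters-only retention to differ in opposite directions, with the relative gap in start rates the larger.

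**Illustrations (all rates assumed).**

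| s_F, r_F | s_P, r_P | D_c | Retained among enrolled, F v P | D_e |
|---|---|---|---|---|
| 80%, 60% | 50%, 70% | -10 points | 0.80 x 0.60 = 48% v 0.50 x 0.70 = 35% | +13 points |
| 80%, 70% | 60%, 75% | -5 points | 56% v 45% | +11 points |
| 50%, 80% | 80%, 60% | +20 points | 40% v 48% | -8 points |
| 60%, 75% | 60%, 70% | +5 points | 45% v 42% | +3 points |

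In the first row, 0.80/0.50 = 1.60 exceeds 0.70/0.60 = 1.17, so the sign reverses. The third row reverses the other way. The fourth has equal start rates and does not reverse.

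**Range with no effect on anyone's persistence.** Suppose that 50% to 70% of enrolled participants start under either route and 80% of them are retained in both groups. Fair screening adds a further 10% to 30% who start only because of it, and 40% to 60% of these are retained.

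- Smallest starters-only gap: (0.70 x 0.80 + 0.10 x 0.60) / 0.80 = 77.5% v 80%, or -2.5 points.
- Largest: (0.50 x 0.80 + 0.30 x 0.40) / 0.80 = 65% v 80%, or -15 points.
- Among enrolled, the difference is the added share times its retention: from 0.10 x 0.40 = +4 points to 0.30 x 0.60 = +18 points.

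If the added starters are retained as well as the rest (80%), the starters-only difference is 0, while the enrolled difference is +8 to +24 points (0.10 x 0.80 to 0.30 x 0.80).

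**The case against.** **The two sections do not contradict each other.** The outcome section defines the measure, and the analysis section may simply refer back to it in shorter form. This stands: the analysis section is ambiguous, and a reader who infers a direct contradiction goes beyond the text. But if the outcome section governs, the conditioning on starting treatment is confirmed.

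**Linkage is reported beside retention.** A reader would see both proportions and could multiply them, and retention among those linked is a legitimate descriptive quantity. This also stands, and it limits the harm. It does not change what a model fitted to starters would test.

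**Selection remains with all enrolled.** Enrolment follows PHC randomisation and requires passing initial screening, attending confirmatory screening at the PHC and consenting. This is correct. An all-enrolled denominator removes one layer of selection, not all of it.

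**Detail of this kind is often left to a fuller document.** That is fair for a denominator left unstated. Here the article does fix one, and it is the problematic one.

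Two stronger readings are tempting but unsupported. A reader might infer that starters found at fairs are more selected because they were not seeking care. Nothing in the document shows this, and fair-screened enrolees have already attended the PHC for confirmatory screening. A reader might also take the planned comparison to be between randomised screening arms. As written it is by place of first screening, and participants in the enhanced condition may be screened at either place.

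**Conclusion.** The point holds as a minor one. The only explicit retention denominator is starters, which conditions the comparison on the linkage outcome, and the analysis section does not settle whether that denominator or all enrolled is meant.

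The starters-only result can misstate retention among enrolled participants and can reverse its sign, for or against fair screening. It need not do so: equal start rates rule out a reversal. The document gives no basis for saying that a reversal is likely or which group it would favour. The sizes shown (for example -10 v +13 points) rest wholly on assumed rates.

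The primary screening count, which has the PHC as unit of analysis, and the intervention analyses are unaffected.

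**What to change.** 1. **Denominator.** In Outcome measures and schedule and in the Screening analysis, define the compared retention outcome as having begun treatment and remained in care to study end. Use all enrolled participants as denominator and count non-starters as not retained. Report retention among starters as descriptive.
2. **Contrast, as a separate and explicit change.** Make this comparison by randomised screening condition (enhanced v standard PHCs), since place of first screening does not coincide with it. Keep fair v PHC as descriptive.
3. **Limit to state.** Note that selection into enrolment remains, because enrolment follows PHC randomisation.

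The cost is about one sentence in each section for the first change and one more for the second. No new data are needed, since starting treatment and retention are already measured and each PHC's condition is known. The named model can stay. Assessments were ongoing at the date given under Current status of the study; the choice should be recorded before these results are examined.
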